### Analyses

Data will be analyzed according to the CONSORT statement [40]. A detailed statistical analysis plan will be prepared and finalized before breaking the blind. Descriptive statistics will be determined for the intention-to-treat population according to treatment assignment. The intention-to-treat population consists of all randomized patients. The primary hypothesis is that the intervention is superior to treatment as usual according to the number of days with substance use within the past 30 days 6 months after the end of the intervention (*t*_3_). A mixed negative binomial regression will be performed based on the intention-to-treat population with treatment group, time, interaction between treatment group and time, and recruitment center as fixed effects, the number of days with substance use within the past 30 days at baseline as a covariate, and patient and therapy group as random effects. The contrast of the treatment group at *t*_3_ will be interpreted in a confirmatory manner. We will report adjusted group differences with corresponding 95% confidence intervals and *p* values. Mixed models are more robust against missing values than models without random factors and yield unbiased estimates under the missing at random assumption. For model diagnostics, a systematic examination of factors associated with loss to follow-up will be conducted. Missing values will be imputed in a sensitivity analysis by the multiple imputation method. Additionally, the primary analysis will be conducted on the per protocol population. The following subgroup analyses will be planned. The secondary outcomes will be analyzed in an exploratory manner with appropriate models with the same covariates and fixed and random effects as in the primary analysis. Multiple mediation models for identifying the mechanisms of intervention effects (with a focus on behavioral measurements of self-regulation and mindfulness) will be used [77]. The safety end points will be determined with a mixed logistic regression. Interim analyses are not planned. The two-sided type I error will be set at 5%. Statistical analyses will be carried out with SPSS, Version 21 (IBM Corp., Armonk, NY).

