### Measurement

Participants are asked questions in structured clinical interviews and they complete questionnaires. Their hands are scanned so that we can calculate the 2D:4D ratio (*t*_0_ only), and they undergo a computerized assessment for several neuropsychological tasks at four points within the study process: after detoxification and before randomization and the following SUD treatment phase (*t*_0_), 4 weeks into treatment (*t*_1_), 8 weeks after *t*_0_ (*t*_2_), and 6 months after *t*_2_ (*t*_3_). Figure 1 gives an overview of the measures used.

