The intervention group receives a mindfulness-based group intervention consisting of 12 45-min sessions relating mindfulness techniques to substance use problems in adolescents. In each of the first 4 weeks of the intervention, the participants receive two 45-min sessions of the core mindfulness-based group intervention. At the end of the 4 weeks, they undergo the first interim assessment (*t*_1_). In weeks 5–8 of treatment, intervention group participants receive one weekly 45-min session of the sustained mindfulness-based group intervention (maximum of four sessions). After the total mindfulness-based group intervention and after 8 weeks of treatment, participants undergo another assessment (*t*_2_), which is followed by the final assessment (*t*_3_) 6 months after *t*_2_. Assessments for *t*_3_ are performed by study personnel and participants receive €50 and travel expenses as compensation for participation in the *t*_3_ assessment. The mindfulness-based group intervention is delivered by clinically experienced researchers, who are currently in therapeutic training or have finalized therapeutic training, and are experienced in giving mindfulness-based interventions. Figure 2 gives an overview of the study flow.

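### The primary model gives baseline use days one slope at all visits; the t3 contrast is biased if that slope changes after treatment and baseline-related dropout differs by arm

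*Protocol article*

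**What the plan says.** The Analyses section of the protocol article specifies the primary model as a mixed negative binomial regression in all randomised patients. Its mean structure consists of treatment, visit and their interaction, followed by "recruitment center as fixed effects, the number of days with substance use within the past 30 days at baseline as a covariate". Random effects are named for the patient and for the therapy group. The only interaction listed is treatment by time. The treatment contrast at t3 "will be interpreted in a confirmatory manner"; it is the single confirmatory test. The same section says that mixed models "yield unbiased estimates under the missing at random assumption", with no condition attached. It plans multiple imputation as a sensitivity analysis, an examination of what predicts dropout, and a detailed SAP before unblinding.

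On timing, Measurement places t1 at "4 weeks into treatment", and Procedure says of t2 that "after 8 weeks of treatment, participants undergo another assessment". Under Sample, that treatment is inpatient or day care. The final visit, t3, is 6 months after t2. Baseline use refers to the 30 days before detoxification (Primary outcome).

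**The concern.** Treatment may act differently at each visit in this model; baseline use may not. Use before detoxification may well predict use days during supervised treatment differently from use days half a year later. A common slope is then a compromise, and with two in-treatment visits against one follow-up visit it is pulled away from its t3 value.

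With everyone observed, randomisation balances baseline use and the wrong slope does little harm. With dropout, the patients still observed at t3 may differ in baseline use between the arms, and correcting for that is the covariate's job. If its slope is wrong at t3, part of the imbalance passes into the treatment contrast. This can happen under missing at random, the condition that the article says the model handles. More patients would not remove it.

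**Working it through.** **1. The article's own figure.** Sample size calculation: d = 0.36, two-sided alpha 0.05, 80% power, 1:1. The two-sample t-test (noncentral t) gives 123 per arm, 246 in total, power 80.3%. The stated figure reproduces. It uses no baseline adjustment, so the present point does not change it.

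**2. Are t1 and t2 in the model?** The text does not say so outright. With baseline as a covariate, a treatment-by-time interaction needs at least two post-baseline visits. Measurement also schedules structured interviews at all four time points, and the Timeline Followback is an interview. The inference is strong but remains an inference.

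**3. Precision with complete data.** Let rho be the correlation of baseline with the t3 outcome, and f the fitted slope as a fraction of the true t3 slope. On a continuous scale the relative residual variance is 1 - 2f·rho² + f²·rho². For rho = 0.5 and f = 1/3: 1 - 0.167 + 0.028 = 0.861. Power at 123 per arm:

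| rho | f = 0 | f = 1/3 | f = 1/2 | f = 1 |
|---|---|---|---|---|
| 0.3 | 80.3% | 82.3% | 82.9% | 83.8% |
| 0.5 | 80.3% | 85.8% | 87.7% | 90.1% |

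A slope that is too shallow gives up some of the gain from adjustment, but power does not fall below the planned 80%.

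**4. Bias with dropout: a rough formula.** Let b3 be the true t3 slope, b the fitted common slope, and D the difference in mean baseline days (intervention minus control) among patients observed at t3. Then the bias in the t3 log rate ratio is about (b3 - b) × D. It is near zero if b = b3, or if D is near zero, as with complete data or with the same dropout dependence in both arms.

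**5. Simulation, first set of inputs (all assumed).** 123 per arm; negative binomial with patient random intercept (SD 0.7, dispersion 1); visit means about 2, 2 and 10 days; baseline SD 7.4 days; slope per baseline day 0 to 0.02 at t1/t2 and 0.05 to 0.06 at t3; no true effect.
- Moderate (dropout rises with baseline use in the intervention arm; 27% v 25% missing): D = 19.0 - 20.0 = -1.0 day. With b between 0 and b3, the formula limits the bias to -0.05 to -0.06. The simulated shift against the model with baseline × time was -0.030 to -0.039. With equal slopes it was -0.002.
- Extreme (opposite dropout patterns by arm; 29% missing): D = 18.6 - 21.5 = -2.9 days, so the limit is -2.9 × 0.05 = -0.145 to -2.9 × 0.06 = -0.174. Simulated bias was -0.07 to -0.17, with false-positive rates of 4% to 16% across settings. With baseline × time, bias was 0.00 to 0.02 and the rate 3% to 6%. There were 160 trials per setting, so the Monte Carlo SE at 5% is √(0.05 × 0.95/160) = 1.7 points.

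**6. Simulation, second set of inputs (all assumed).** Log slopes per baseline SD at t1/t2/t3 of 0.5/0.5/0.5, 0.2/0.2/0.5 or 0/0/0.5; about 27% missing at t3. With N = 40,000:
- Equal slopes: the two models agree under every dropout pattern.
- Unequal slopes: the common slope was fitted at 0.28 to 0.31 (0.2/0.2/0.5) or 0.13 to 0.20 (0/0/0.5), against a true 0.5 at t3.
- Baseline-dependent dropout in one arm only: the models differ by about -0.04 to -0.08. In opposite directions: about -0.09 to -0.15.

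At N = 246, slopes 0/0/0.5, no true effect, 400 trials:

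| Dropout | Mean log RR, common / by visit | Type I error, common / by visit |
|---|---|---|
| None | -0.012 / -0.010 | 5.8% / 4.3% |
| Same in both arms | -0.009 / -0.008 | 6.8% / 4.8% |
| One arm only | -0.087 / -0.008 | 8.7% / 6.8% |
| Opposite | -0.162 / -0.009 | 13.3% / 5.5% |

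The Monte Carlo SE of these rates is about 1.1 to 1.7 points. With complete data the SD of the estimate was 0.180 with the common slope and 0.174 with visit-specific slopes; power at a log rate ratio of -0.55 was 87% and 88%.

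Neither set included the therapy-group random effect, and no 30-day ceiling on the outcome is stated for either.

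**The case against.** The best case for the plan is that covariate-by-visit terms and the coding of time are normally settled in the SAP, which the article promises. The article does not exclude the term, and every likelihood analysis needs a correct mean model, so the missing-at-random sentence is common shorthand. Moderate shifts are small: 0.04 against a standard error near 0.195 is about 0.2 standard errors. The 13% to 16% error rates need opposite dropout patterns in the two arms. The planned look at predictors of dropout and the multiple imputation would also help.

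Much of this stands, and it sets the weight of the point. It does not remove it. The article names the model's terms, and a SAP that follows them as written would keep the common slope. Imputation protects only if the imputation model itself has visit-specific baseline effects, and it is a sensitivity analysis, not the confirmatory one.

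A reader might infer more than the documents support:
- That the t3 contrast is under-adjusted as a matter of fact. No slopes are given. If the t3 slope were shallower than the in-treatment slope, the model would over-adjust and the bias would reverse.
- That the missing-at-random claim is simply false. It fails here only when unequal slopes and arm-specific, baseline-dependent dropout occur together. Unblinded patients and extra sessions in one arm make such dropout conceivable, but nothing in the documents shows it.
- That power is at risk. Step 3 shows otherwise.
- That centre also needs a time interaction. Randomisation is stratified by centre, and the calculations did not test such a term.

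**Conclusion.** The point holds in conditional form, as a minor to moderate improvement. The listed model constrains baseline use to one slope across in-treatment and follow-up visits, which is doubtful given the visit schedule. If the slopes are equal, nothing is lost. If they differ and data are complete, or dropout depends on baseline alike in both arms, the contrast is essentially unbiased and only some precision is given up. If they differ and baseline-dependent dropout also differs by arm, the sole confirmatory contrast is biased. The size is about 0.03 to 0.08 on the log rate ratio in moderate cases, a distortion of the rate ratio of roughly 3% to 8% (exp(-0.03) = 0.97, exp(-0.08) = 0.92). In extreme cases it reaches about 0.17 (exp(-0.17) = 0.84). In the simulated cases, with a steeper t3 slope, the bias favours the arm that loses more heavy users. Slopes, means, dispersion and dropout patterns are all assumptions, and the inclusion of t1 and t2 in the model is inferred.

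**What to change.** In the Analyses section and the SAP:
- state which visits enter the model and treat time as categorical;
- add baseline use days × time to the fixed effects and take the confirmatory t3 treatment contrast from that model, or justify leaving the term out;
- give baseline use visit-specific effects in the multiple-imputation model;
- make the missing-at-random sentence conditional on a correctly specified model.

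With three post-baseline visits this adds two parameters and a line or two of text. No new data are needed and the sample size is unchanged. In the simulations the added term carried no material loss of precision, and it can be fixed in the SAP before the blind is broken.

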Preliminary evidence from research-informed treatments links self-regulatory models of SUD to mindfulness-based approaches, because mindfulness targets several aspects of self-regulation [6, 12, 13, 17]. Mindfulness is defined as bringing full awareness to present-moment experiences in an accepting, non-judgmental, and open-minded way [18]. Mindfulness skills are associated with cognitive and affective stability and flexibility, adaptive coping, and reduced cue-reactivity towards stress-induced cravings [12, 19]. Initial neuroimaging [19, 20] and clinical studies [21] provide evidence that mindfulness skills can help SUD patients. Mindfulness brings attention to highly automated and minimally controlled habits, which are often involved in craving and substance use relapse. Mindfulness practice can help people to become aware of craving and substance use habits. This opens opportunities for modifying reactions instead of following established stimulus–response behaviors, which may involve modifying unpleasant sensations or emotions with substance use. This could reduce the risk of relapse in SUD patients.

Sanger and Dorjee [22] produced strong neuropsychological evidence for the positive effects of mindfulness practice in adolescence. Affective self-regulation and coping skills were enhanced by changes in prefrontal brain functioning. The current literature suggests that mindfulness practice impacts affective stability and attentional control and may, therefore, be useful in SUD treatment [23].

The effects of mindfulness-based interventions in adult clinical populations are well documented. Mindfulness-based interventions target different patient groups, such as mindfulness-based stress reduction for chronically ill patients [24, 25], mindfulness-based cognitive therapy (MBCT) for depressed patients [26] and mindfulness-based relapse prevention (MBRP) for SUD patients [27–29]. Even in comparison to active control groups, these interventions were able to reduce legal and illegal substance use [30–32], cravings [13, 17], and relapse rates [30–32]. Up to now, no unwanted side effects of mindfulness-based interventions have been reported for relevant target groups.

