### Procedure

The procedures in the current study have been approved by the ethics board of Ruhr University Bochum (176268). During participant recruitment and treatment, two study centers (Hamm and Hamburg; Hamm is the coordinating center) will provide a mindfulness-based group intervention in addition to what is routinely provided as standard inpatient SUD treatment. Patients admitted to either study center because of SUD treatment and who have completed detoxification are given information about the study and their possible participation if they are eligible for study participation according to the inclusion and exclusion criteria. After written informed consent is given by both the patient and their parent or guardian, the *t*_0_ assessment will be performed within 1 week after the transition from detoxification treatment to after-detoxification treatment. After the *t*_0_ assessment, patients will be randomized to either the intervention group (mindfulness-based group intervention in addition to standard treatment) or the control group (standard treatment as usual). The patients will be randomly allocated to either the Mind It! group or the control group in a 1:1 allocation ratio, stratified by study center with variable block lengths. The randomization lists will be prepared by the Department of Medical Biometry and Epidemiology of the University Medical Center Hamburg-Eppendorf. The central allocation procedure is managed by the coordinating study center in Hamm to guarantee allocation concealment.

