### Safety

A set of adverse events (AEs) and serious adverse events (SAEs) were defined and their prevalence and any possible causal relation to the new mindfulness-based group intervention under evaluation were tracked. All AEs and SAEs, from the first mindfulness-based group intervention to 28 days after the last mindfulness-based group intervention, will be documented in the patient’s file. Each AE and SAE will continue to be monitored until the event has terminated and the participant’s state has improved or at least proved to be stable but no longer than 3 months after the end of the participant’s treatment. The study team will evaluate any possible causal relationship between AEs and SAEs and participation in the mindfulness-based group intervention and documents this.

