### Sample size calculation

Based on prior research [29, 31, 32], we expect to detect a small to medium-sized effect of *d* = 0.36 for our primary outcome. We calculated the sample size using G*Power [76], with a two-sided alpha level of 0.05 and a study power of 80%. The required sample will comprise 246 participants (123 both in the control group and in the intervention group). To achieve this sample size, we seek to screen *N* = 340 patients for eligibility for the trial (Fig. 1).

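### The only safety model named, a mixed logistic regression, has no provision for rare events and gives no finite odds ratio when an arm is empty

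*Protocol article*

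**What the plan says.** The Analyses section of the protocol article gives safety one sentence: "The safety end points will be determined with a mixed logistic regression". It states no condition, exception or fallback for sparse data. It does not name the test (Wald, score or likelihood ratio), the estimation method, or the random effects in this model. The same section plans descriptive statistics by assigned arm, sets a two-sided 5% level, and announces a fuller SAP to be completed before unblinding. That SAP is not shown.

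The Safety section says that adverse and serious adverse events are recorded and that "any possible causal relation to the new mindfulness-based group intervention under evaluation were tracked". It gives the causality judgement to the study team. The Background says that so far "no unwanted side effects of mindfulness-based interventions have been reported for relevant target groups". The article gives no expected event rate for either arm.

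**The concern.** A maximum-likelihood logistic model performs worst when events are few, and the authors themselves expect little harm from mindfulness. If one arm has no events for an end point, the estimated odds ratio runs to infinity (or zero) and the interval has one open end. If neither arm has an event, there is nothing to estimate. The Abstract expects the trial to support a safe treatment option. Such a claim rests on absolute risks with limits: how many patients were affected in each arm, and how large a risk the data still allow. The named model gives neither figure when an arm is empty.

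**Working it through.** **Arm size.** The Sample size calculation section uses d = 0.36, two-sided alpha 0.05 and 80% power; the Procedure section allocates "in a 1:1 allocation ratio, stratified by study center with variable block lengths". The normal approximation gives n = 2(1.960 + 0.842)²/0.36² = 2 × 7.849/0.1296 = 121.1, so 122 per arm. The noncentral t calculation gives 122.09, rounded up to 123 per arm and 246 in total, with power 80.3%. The article's figure is reproduced. It was set for the primary outcome and serves here only as the arm size.

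**How often would an arm be empty?** With the same true rate p in both arms, P(at least one empty arm) = 1 − [1 − (1 − p)^123]². The rates are assumptions.

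| Assumed rate | P(a given arm is empty) | P(at least one empty) |
|---|---|---|
| 0.5% | 0.995^123 = 0.540 | 79% |
| 1% | 0.99^123 = 0.290 | 50% |
| 2% | 0.98^123 = 0.083 | 16% |
| 5% | 0.95^123 = 0.002 | 0.4% |

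Both arms are empty with probability 0.290² = 8% at a 1% rate and 0.540² = 29% at 0.5%. If all 340 patients mentioned in the Abstract were randomized (170 per arm), the chance of at least one empty arm falls to 1 − (1 − 0.99^170)² = 1 − 0.819² = 33% at 1%, and 1 − (1 − 0.98^170)² = 1 − 0.968² = 6% at 2%.

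**What the model returns for 6/123 versus 0/123.** This split is an illustration; it is not in the article. The odds ratio is (6 × 123)/(117 × 0), which is infinite. In a plain logistic fit by Newton iteration, the result depends on where the iteration stops:

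| Steps | log OR | SE | Wald p |
|---|---|---|---|
| 8 | 6.23 | 9.0 | 0.49 |
| 15 | 13.23 | 297.5 | 0.96 |
| 20 | 18.23 | 3,624 | 0.996 |
| 25 | 23.23 | 44,150 | 0.9996 |

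A random-intercept version, with assumed therapy groups of eight in the intervention arm, was fitted to three simulated placements of the six events. Two gave Wald p of 0.999 and 0.996. The third diverged.

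**Other tests on the same 6 versus 0.**
- Fisher exact: 2 × (123/246)(122/245)(121/244)(120/243)(119/242)(118/241) = 2 × 0.0147 = 0.029.
- Pearson (score): 246 × 36/(6 × 240) = 6.15 on 1 df, p = 0.013.
- Likelihood ratio from the plain logistic model: 2 × [−23.97 − (−28.21)] = 8.47 on 1 df, p = 0.0036.
- Firth-penalised logistic: odds ratio 13.7, profile-likelihood p = 0.012, Wald p = 0.077.

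With 170 per arm the Fisher and likelihood-ratio values are almost the same, 0.030 and 0.0037. At 5 versus 0 the choice of test decides significance: Fisher 0.060, score 0.024, likelihood ratio 0.008.

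**What can be reported instead.** The risk difference for 6 versus 0 is 6/123 = 4.9%, with a Newcombe 95% interval of 0.9% to 10.2%. For 0/123 the exact upper limit of the two-sided 95% interval is 1 − 0.025^(1/123) = 2.95%.

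**Limit of the problem.** A single control event restores a finite plain logistic estimate. For 6 versus 1, Wald p = 0.092 and Fisher p = 0.12; for 8 versus 1, Wald p = 0.045 and Fisher p = 0.036.

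**The case against.** The strongest reply is that the test, the estimation method and the handling of sparse data are ordinary SAP content, and the article announces an SAP. Logistic regression is a normal choice for a yes/no end point. This has weight, and it is why the point is minor. It does not remove it: the article did not leave the safety method open but named one model without exception, and an SAP that follows that sentence inherits the limitation.

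The second reply is that rarity is not shown. This stands. The Background statement concerns side effects of mindfulness, whereas the Safety section records all adverse events in adolescents in inpatient or day treatment, and these may be common. At about 5% per arm or more the problem practically disappears.

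Third, harm has other routes to notice: the planned descriptive statistics by arm, the study team's causality review, and a data and safety monitoring board that meets twice a year. This stands too.

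A reader might draw three stronger conclusions, and the article supports none of them.
- *That a split such as 6 versus 0 would be reported with p near 1.* This needs a Wald test, which the article does not name. The likelihood-ratio and score tests both fall below 5%.
- *That events judged related to the mindfulness group put a zero in the control cell by construction.* The article does not say that such events enter a two-arm model; causality review is described as a separate step.
- *That the patient and therapy-group random effects cannot be estimated.* The article lists those effects for the primary analysis and carries them over to the secondary outcomes. It does not specify them for safety, nor does it say that each patient contributes a single yes/no outcome.

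**Conclusion.** The point holds as a minor one. The article fixes a single safety model that yields no finite odds ratio or two-sided interval when one arm is empty, and no bound on risk when both are. Choosing a better test repairs the p value but not the missing estimate. How often this would arise depends on assumed event rates: at 123 per arm, about an even chance per end point at 1%, about one in six at 2%, and negligible at 5%. Nothing here shows that a harm signal would be hidden, and no stated figure is wrong. The unseen SAP may already deal with it.

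**What to change.** Replace the safety sentence, or qualify it in the SAP before unblinding, along these lines: *For each safety end point, the number of patients with at least one event will be reported per arm as n/N, with the risk difference and its 95% confidence interval (Newcombe or exact). Where events are sparse, the arms will be compared by Fisher's exact test or by Firth-penalised logistic regression. The mixed logistic model will be used for end points with enough events in both arms. Events judged related to the mindfulness group will be reported for the intervention arm only, with an exact confidence interval.*

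The SAP should choose between Fisher and Firth in advance and state the event threshold, so that neither is decided after seeing the data by arm. If Firth is chosen, it should specify profile-likelihood inference, since the penalised Wald test gave 0.077 where the profile test gave 0.012.

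The cost is wording; no extra data or patients are needed. The downside is small: the exact comparison ignores center and therapy-group clustering and is conservative.
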